# The Disruptive bEhavior manageMEnt ANd prevention in hospitalized patients using a behaviORal intervention team (DEMEANOR) study protocol: a pragmatic, cluster, crossover trial

**DOI:** 10.1186/s13063-020-04278-2

**Published:** 2020-05-24

**Keywords:** Behavioral intervention team, Disruptive behavior, Hospitalized patients, Advanced practice registered nurse, Social work intervention

## Abstract

**Background:**

Disruptive behavior in hospitalized patients has become a priority area of safety concern for clinical staff, and also has consequences for patient management and hospital course. Proactive screening and intervention of patients with behavioral comorbidities has been reported to reduce disruptive behavior in some settings, but it has not been studied in a rigorous way.

**Methods:**

The Disruptive bEhavior manageMEnt ANd prevention in hospitalized patients using a behaviORal intervention team (DEMEANOR) study is a pragmatic, cluster, crossover trial that is being conducted. Each month, the behavioral intervention team, comprising a psychiatric-mental health advanced practice nurse and a clinical social worker, with psychiatrist consultation as needed, rotates between an adult medicine unit and a mixed cardiac unit at Vanderbilt University Medical Center in Nashville, TN, USA. The team proactively screens patients upon admission, utilizing a protocol which includes a comprehensive chart review and, if indicated, a brief interview, seeking to identify those patients who possess risk factors indicative of either a potential psychological barrier to their own clinical progress or a potential risk for exhibiting disruptive, aggressive, or self-injurious behavior during their hospitalization. Once identified, the team provides interventions aimed at mitigating these risks, educates and supports the patient care teams (nurses, physicians, and others), and assists non-psychiatric staff in the management of patients who require behavioral healthcare. Patients who are both admitted to and discharged from either unit are included in the study. Anticipated enrollment is approximately 1790 patients. The two primary outcomes are (1) a composite of objective measures related to the patients’ disruptive, threatening, or acting out behaviors, and (2) staff self-reported comfort with and confidence in their ability to manage patients exhibiting disruptive, threatening, or acting out behavior. Secondary outcomes include patient length of stay, patient attendant (sitter) use, and the unit nursing staff retention.

**Discussion:**

This ongoing trial will provide evidence on the real-world effectiveness of a proactive behavioral intervention to prevent disruptive, threatening, or acting out events in adult hospitalized patients.

**Trial registration:**

ClinicalTrials.gov: NCT03777241. Registered on 14 December 2018.

## Background

Patients who are hospitalized on non-behavioral health units who exhibit concurrent psychiatric comorbidities can be at risk for increased length of hospital stay due to the complexities associated with treatment, as well as behaviors that can be difficult to address by staff. Research has substantiated that 20–40% of patients hospitalized on general medical-surgical units have a psychiatric diagnosis [4, 7]. At our institution, 54% of all discharges on two medical-surgical units during fiscal year 2017 had a behavioral health diagnosis. These patients had a 25% longer mean length of stay (6.6 days vs 5.31 days without a behavioral health diagnosis) and 17% higher mean variable costs per discharge ($11,307 vs $9642), based on 104,843 total patient days.

At the same time, an internal “Behavioral Health Care Knowledge and Skills” assessment of 623 staff nurses identified that 72% reported patients’ behavior impacted their ability to provide care, 58% reported experiencing situational anxiety in caring for these patients, 56% reported caring for behavioral health patients daily to weekly (32% reported monthly), 50% reported feeling somewhat to very uncomfortable caring for these patients, and 44% feared for their personal safety as a result of patient disruptive behavior. These data demonstrate a large impact of patient behavior on the care that can be provided to them and on the satisfaction and morale of nursing staff.

Additionally our institutional data suggest nursing turnover rate is higher for those units with a higher burden of patients with behavioral comorbidities, and exit interviews suggest a link between turnover and the challenges of managing patients exhibiting disruptive behavior. Beyond turnover, there is considerable transfer from these units as nurses seek to improve their job satisfaction. Given the impact on patient care as well as on those providing care, identifying effective strategies for preventing and managing disruptive patient behavior has become a priority in promoting staff and patient safety.

Several academic medical centers have reported numerous benefits with the use of a behavioral intervention team (BIT), which provides proactive consultation and liaison psychiatric service. Observed outcomes included decreased length of stay and decreased use of constant companions (sitters) [4, 7, 8, 11, 13, 14]. However, most reports are anecdotal, and there is a lack of comparative effectiveness research supporting the impact of proactive measures to reduce disruptive behavior in hospitalized patients.

The aim of the present trial is to evaluate the impact of a BIT on one medical-surgical unit and a mixed cardiac care unit with a high proportion of patients with behavioral health comorbidities. We hypothesize that, when compared to usual unit staffing, the addition of a dedicated, trained BIT provides meaningful improvement in the prevention and management of disruptive behavior in the healthcare setting as well as improvement in staff perceptions of their ability to manage patients exhibiting disruptive, threatening, or acting out behavior.

## Methods

This manuscript was written in accordance with the Standard Protocol Items: Recommendations for Interventional Trials (SPIRIT) guidelines [2].

### Design

The Disruptive bEhavior manageMEnt ANd prevention in hospitalized patients using a behaviORal intervention (DEMEANOR) study is a single-center, pragmatic, cluster, crossover trial, testing the superiority of the BIT program to usual care, beginning 1 March 2019 on one medical-surgical unit and one mixed cardiac care clinical unit at Vanderbilt University Medical Center in Nashville, TN, USA. The BIT is deployed to each unit in alternating months, as shown in Fig. 1. Patients presenting to the unit during a month when the team is present contribute to the intervention arm, while those presenting to a unit when the team is not present contribute to the control arm.

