### Enrollment/randomization

Patients presenting to and discharged from participating units are enrolled automatically. As a cluster, crossover trial, randomization was limited to which unit the intervention would be deployed to first. Unit nursing staff were invited to participate in online surveys by e-mail, with reminders through staff meetings; their participation is voluntary.

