All unit staff will be exposed to the intervention throughout the study, although after the first month of the study only those staff on the unit initially randomized to the intervention will have been exposed. This provides an opportunity for a comparison between exposed and unexposed staff. We note that patients present on the unit during the time of crossover are exposed to both the intervention and the control conditions. To avoid crossover effects and eliminate the logistical challenges of changing any behavioral care provider team during the admission, patients are excluded if they are present on a unit during crossover. This does lead to some possibility of contamination, since the BIT may be present in a unit during a control condition. However, the BIT comprises just two providers who were given strict instructions to avoid such contamination and who were also provided with training on how to defer questions or requests that would have resulted in contamination.

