### Power calculation

Approximately 17.5% of patients admitted to the two participating units required one or more of the behavioral interventions in the year prior to the study. To determine the number of months of data collection necessary to detect a reduction of 5% in the use of behavioral interventions between the intervention and control arms, we used the method described by Arnup et al. [1]. Based on patient length of stay and admit rates, we estimated between 89 and 105 patients would be eligible for inclusion each month (patients present on a unit at crossover will not be included in the analysis). Therefore, a cluster size of 90 was used. If the within-period correlation is 0.1 and the within-cluster within-period correlation is also about 0.1, we would achieve 80% power with 10 months of data collection (a total sample size of 1790 patients exposed to either the control or intervention arm). Since these estimates are based on assumptions, and it is possible that either a shorter or longer duration is needed, we have specified an interim analysis at 6 months to confirm the overall event rate and to estimate the observed correlations. No comparisons between groups will occur at this time; accrued data will be used only for sample size re-estimation.

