## Discussion

Upon completion, the DEMEANOR study will provide the most comprehensive data to date on the impact of a proactive behavioral intervention on disruptive, threatening, or acting out events in adult hospitalized patients.

Several potential threats to the validity of the trial exist. As the primary and secondary variables are being collected from documentation in the EHR, the potential for incomplete data exists. Additional limitations in using EHR data in clinical research include ensuring data security and privacy and overcoming challenges associated with linking clinical data from diverse systems [3]. The use of sitters or virtual sitters and restraints is dependent on a variety of patient care conditions, and verifying those that pertain to disruptive patient behavior will be dependent on clinical documentation or specific ordering directives.

There is a possibility that patients hospitalized during the study period who did not receive a specific consult from the behavioral intervention team (BIT) nonetheless benefited from the presence of the team. The study design does not allow a conclusive differentiation between a spillover effect on the units where the BIT is implemented and a possible secular trend from other unmeasured influences on the primary or secondary outcomes. Consults on the control unit during the study period will be monitored to assess for the potential for an increase due to staff awareness and exposure to the BIT during the crossover periods. Potential fluctuations in patient census during the trial and also the number of patients presenting with behavioral comorbidities or those exhibiting disruptive behavior may also impact the study results.

Nursing response rates to the pre-study, 1 month, and post-implementation surveys may impact the ability to evaluate change in perceptions of their ability to manage patients exhibiting disruptive, threatening, or acting out behavior. Also, nursing retention rates are dependent on a number of factors, including career opportunities which may not be related to nursing job dissatisfaction or to encountering patients with disruptive behavior.

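### A patient's arm follows the unit reached while the BIT's location is predictable, and no described safeguard covers placement; preferential placement of high-risk patients could mask part of the effect

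*Protocol article*

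**What the plan says.** The Design section ties arm to unit and month: "Patients presenting to the unit during a month when the team is present contribute to the intervention arm". Under Enrollment/randomization, the only random element is which unit received the team first, and "Patients presenting to and discharged from participating units are enrolled automatically". After that the team alternates monthly.

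Three protections against contamination are described:

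- **Intervention section:** "the BIT comprises just two providers who were given strict instructions to avoid such contamination". They were also trained to defer requests that would cause contamination.
- **Population section:** patients present on a unit at a crossover are left out of the analysis.
- **Discussion section:** consults on the control unit are monitored.

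Statistical analysis principles adjusts the patient model for age, sex, race, comorbidities, reason for admission and psychiatric diagnoses. Presentation of the results promises baseline characteristics by treatment group. The Discussion also warns that "the number of patients presenting with behavioral comorbidities or those exhibiting disruptive behavior may also impact the study results", in the context of fluctuation during the trial.

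**The concern.** Patients enter after the allocation of both units is settled and foreseeable. A team whose task is to help with psychiatric and behavioral problems gives a plausible reason to place a difficult patient where the team is. That would be recruitment bias after allocation. It would raise the underlying risk of the BIT arm and, where the patient would otherwise have gone to the other study unit, lower that of the control arm.

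None of the three protections acts on who is placed where. The Discussion treats shifts in behavioral case mix as fluctuation, and does not consider that the BIT calendar could cause them. The covariates include no measure of disruptive behavior shown before arrival, which is what would be likely to prompt such a placement.

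At stake is how a null result is read. It could reflect an ineffective team or a BIT arm at higher risk from the start. The Intervention section says the program is to be scaled if successful, so a false null has consequences.

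**Working it through.** **Inputs from the Power calculation section**

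- Event rate: "Approximately 17.5% of patients admitted to the two participating units required one or more of the behavioral interventions" in the prior year.
- Target: the plan is to "detect a reduction of 5% in the use of behavioral interventions between the intervention and control arms". This is read as 5 percentage points (17.5% to 12.5%), because a 5% relative reduction would need about 58,000 patients.
- Patients per unit-month: "Therefore, a cluster size of 90 was used".
- Power and size: "we would achieve 80% power with 10 months of data collection (a total sample size of 1790 patients" in all.

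**Reproducing the plan's figures**

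Size: 2 units × 10 months × 90 = 1,800, and 1,790 / 20 = 89.5. So 90 is per unit per month.

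Power: assume a two-sided 5% test, since alpha is not stated. Detecting 17.5% against 12.5% with 80% power takes 800 per arm, or 1,600. The cluster-crossover design effect is 1 + (m − 1)ρ − mη, where ρ is the within-cluster within-period correlation and η the between-period correlation. With m = 90, ρ = 0.10 and η = 0.0975 (which rounds to 0.1), it is 1 + 8.9 − 8.775 = 1.125, and 1,600 × 1.125 = 1,800. With both exactly 0.10 it is 0.90, giving 1,440 patients, or about 88% power at 1,790. The stated 80% is therefore reachable, and it is the starting point below.

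**Assumed inputs (not in the documents)**

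- k = 2 or 3 patients a month exchanged one for one between the units.
- Gap of 0.2 to 0.4 between the event risks of the steered and displaced patients.

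**Bias**

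Each exchange moves k × gap expected events out of the control unit and the same number into the BIT unit, so

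bias = 2 × k × gap / 90.

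A power of 80% at 5 points means a noncentrality of 1.96 + 0.84 = 2.80. With bias b in points, power is Φ(2.80 × (5 − b)/5 − 1.96).

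| k | gap | bias (points) | share of 5 points | power, unadjusted |
|---|---|---|---|---|
| 2 | 0.2 | 0.89 | 18% | 63% |
| 3 | 0.2 | 1.33 | 27% | 54% |
| 2 | 0.4 | 1.78 | 36% | 44% |
| 3 | 0.4 | 2.67 | 53% | 26% |

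**Cross-check without exchange.** The base is 90 × 0.175 = 15.75 events per unit-month. Moving 2 patients with risk 0.5 from control to BIT gives 16.75/92 = 18.2% against 14.75/88 = 16.8%, a difference of 1.45 points. Moving 3 with risk 0.6 gives 17.55/93 = 18.9% against 13.95/87 = 16.0%, a difference of 2.84 points. The exchange formula at gaps 0.325 and 0.425 gives 1.44 and 2.83.

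**Variations**

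- *Patients from non-study units only:* one arm changes, so the bias is k × gap / 90, or 0.44 to 1.33 points (9% to 27%).
- *Covariates remove half of the imbalance:* the exchange figures also fall to 9% to 27%.
- *The BIT also lowers risk in the steered patients by the design ratio 12.5/17.5:* with risks of 0.50 and 0.10, the hidden share is 30% (k = 2) to 46% (k = 3), against 36% and 53% in the table.
- *High risk means only a behavioral health diagnosis:* the Background gives 54% of discharges on two units not said to be the study units. If this group held every event, its risk would be 17.5/54 = 32%. A gap of 0.32 gives 29% to 43%. If the others carry 5% risk, the group's risk is (0.175 − 0.46 × 0.05)/0.54 = 0.28, the gap is about 0.23, and the shares are 21% to 31%.

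**The case against.** A reader might infer that beds were steered, or that a third to a half of the effect would be lost. The documents support neither. No passage reports steering or says that those who assign beds follow the BIT's location. General awareness is an inference from the open deployment, the training to defer requests, and the Discussion's concern about staff awareness. A third at k = 2 or a half at k = 3 requires a gap of exactly 0.375, exchange between the two units, and no adjustment. The number moved and the risk gap are assumptions.

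Other points also limit the concern:

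- Study sites describes a mixed cardiac medical-surgical unit and a cardiac stepdown unit, so clinical need probably restricts exchange.
- Population requires admission to and discharge from the unit within the month. On a plain reading, a patient transferred mid-stay from the control unit would not count in the BIT arm, which leaves initial placement as the main route.
- The planned covariates are the usual markers of behavioral risk and would remove part of any imbalance. The baseline table would show imbalance in whatever is measured. So it would be wrong to say that the plan has no handling at all.
- The full protocol, not shown here, may contain a bed-assignment rule.
- The bias runs toward no benefit, so it would not create a false claim of superiority.

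All of this stands, and it reduces the likely size. It does not remove the gap: nothing described acts on placement, and neither the covariates nor the protections capture behavior shown before arrival.

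**Conclusion.** The point holds as a conditional weakness in the design and analysis. Arm depends on the unit reached, the BIT calendar is predictable, and no described safeguard addresses placement. If high-risk patients were preferentially placed on the BIT unit, the patient-level primary comparison would be pulled toward no benefit.

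Under the assumed inputs, the hidden share is roughly a fifth to a half of the 5-point target before adjustment, with power falling from 80% to between about 63% and 26%. It is about half that share if the patients come from outside the two units, and smaller after the planned adjustment. These figures show sensitivity; they do not estimate what happened. A cheap analytic check is worth adding.

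**What to change.** 1. From the existing electronic record query, derive for each patient an indicator of any listed medication dose, or any violence or injurious-behavior entry, time-stamped before arrival on the unit. Add it to the patient-model covariates in Statistical analysis principles.
2. Run the primary model with that indicator as a negative-control outcome, leaving it out of the covariates for that run. The BIT's work on the unit should not affect it, so a difference between arms would point to differential placement. Report admissions and the indicator's prevalence by arm and month, next to the baseline table.
3. State as a limitation that placement was not controlled. Trial status gives the end of enrolment as 30 December 2019, so an instruction to those who assign beds can no longer act.

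The cost is one more time-stamped field, one more covariate and one more table, with no extra patients. The indicator will be noisy: doses before arrival may be continued home treatment, and Data collection says that charting of disruptive behavior was variable before the study fields were added. A null negative control would therefore be reassuring but not conclusive.

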**Fig. 1 Fig1:**
[figure not shown]
Depiction of the study implementation showing the ramp-up period and the crossover of the team between units. The timing of surveys and interim analysis is also shown

### Study sites

The two study units are a 27-bed mixed cardiac medical-surgical unit and a 22-bed cardiac stepdown unit.

### Population

All adult (aged ≥18 years) patients admitted to either of the two units during the study period are eligible for the trial. To prevent contamination between study arms, patients must both be admitted to and discharged from the unit during the study month; patients present on a unit at the crossover will not be included in the analysis. In addition, all nursing staff working in these units during the study are included.

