### Intervention

The integration of the BIT into the unit is not itself a research intervention. Institutional leadership planned to deploy one team as a demonstration project, and to scale it if successful. This provided an opportunity for rigorous evaluation of the team’s effectiveness. The BIT, a multidisciplinary team comprising a psychiatric-mental health advanced practice nurse and a clinical social worker, with psychiatrist consultation as needed, is a modified version of an established model at Yale New Haven Hospital [14]. The team proactively screens patients upon admission to the unit, utilizing a protocol which includes a comprehensive chart review and, if indicated, a brief interview, seeking to identify those patients who possess risk factors indicative of either a potential psychological barrier to their own clinical progress or a potential risk for exhibiting disruptive, aggressive, or self-injurious behavior during their hospitalization. Once identified, the team provides interventions aimed at mitigating these risks through a variety of patient-specific interventions, including:
Psychiatric consultation and recommendations for symptom managementBehavioral plans of care for nurse/patient interactionPsychosocial support and brief psychotherapeutic interventionCurbside consultation for any member of the patient’s healthcare teamPatient advocacy and care coordinationPsychiatric-specific disposition support, including both inpatient and outpatient psychiatric services.

The team also provides education and support to the patient care teams (nurses, physicians, and others) and assists non-psychiatric staff in the management of patients who require behavioral healthcare.

All patients on a unit when the BIT is present will be eligible for BIT services, including those who are already admitted when the team crosses into the unit. During a month when the BIT is not present on a unit, the care and management of patients is not supported with proactive screening and management. Unit staff have access to all psychiatric or behavioral care routinely available in usual care. To ensure continuity of care, patients who continue to require psychiatric support at the time the BIT rotates off the unit will continue to receive care equivalent to the usual care condition. It is anticipated that monthly rotations will occur for 10 to 12 months.

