### Secondary outcomes

Secondary outcomes include the occurrence of each intervention separately, sitter use, use of physical or chemical restraints, patient length of stay, and unit nursing staff turnover (Table 2).

**Table 2 Tab2:** Outcome measures and definitions

Outcome	Definition	How we measure

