***Secondary***		
**Rate of unit nursing staff retention**	Amount of turnover (departure from the organization) experienced on each study unit while the study was conducted	Extracted from human resources records
**Patient length of stay**^**a**^	Number of days a patient spends in the hospital from the time of the order to admit to the time of discharge	Extracted from the electronic health record
**Individual components of the primary outcome:** **• Violence control intervention** **• PRN medications for behavior management** **• Nursing problem of violence risk or injurious behavior**	As above	As above
**Use of restraints**	Use of physical or chemical restraints to control patient behavior	Extracted from the electronic health record
**Use of sitters/patient attendants**	Use of sitters/patient attendants for patient observation	Extracted from the electronic health record

^a^Resource length of stay (RLOS): indicates hospital resource/bed utilization, irrespective of the change in patient status. The measure excludes the time that encounters spend as an “emergency department”-type patient but begins the instant a patient is given an order to admit as an inpatient and ends at discharge. This metric thus includes time a patient is in an emergency department bed, in the post-anesthesia care unit, or other location but has an inpatient status. The metric is viewed by average and median, and adjusted by the total Case Mix Index

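### The analysis set is chosen on length of stay, itself a secondary outcome; if the BIT changes stay, the length-of-stay comparison shrinks and the composite is selected differently by arm

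*Protocol article*

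**What the plan says.** All references are to the protocol article. Under Design, "The BIT is deployed to each unit in alternating months". Under Population, "patients must both be admitted to and discharged from the unit during the study month", and "patients present on a unit at the crossover will not be included in the analysis". Enrollment/randomization and Power calculation repeat the rule. Intervention gives the reason (mixed exposure, and the difficulty of changing behavioral provider during an admission) and states that "patients are excluded if they are present on a unit during crossover".

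LOS is a secondary outcome, defined in Table 2 as "Number of days a patient spends in the hospital from the time of the order to admit to the time of discharge". The Background cites shorter stay among the results that other centers observed with a BIT, and the Intervention section lists among the BIT's tasks psychiatric "disposition support, including both inpatient and outpatient psychiatric services".

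The Power calculation takes account of the exclusion only through the cluster size. Statistical analysis principles adjusts for patient characteristics, and Treatment of outliers foresees non-parametric methods for LOS. The threats to validity in the Discussion do not mention selection on LOS.

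**The concern.** Discharge before the crossover happens after exposure has begun. With arrivals spread evenly over a month of T days, a patient who stays L days is kept with probability 1 − L/T, so the chance of being analysed falls steadily as the stay lengthens. LOS is thus both an outcome and the filter for entry into the analysis.

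If the BIT shortens a stay, that patient becomes more likely to be analysed in an intervention month than the same patient in a control month. Two things follow. No analysed stay on the unit can exceed the days left at arrival, so a difference in LOS is compressed. And if patients with behavioral events stay longer than others, the two arms retain different proportions of them, which disturbs the composite primary outcome. Adjustment for baseline covariates and rank-based tests do not undo selection on a post-exposure variable.

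**Working it through.** **Inputs from the article.** Mean LOS 6.6 days with and 5.31 days without a behavioral health diagnosis, and 54% with one (Background); 27 and 22 beds (Study sites); 89 to 105 eligible patients a month, 17.5% event rate and a 5% reduction, read here as 5 percentage points (Power calculation).

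**Assumptions.** Uniform arrivals; a month of 30 or 30.4 days; the Background stays apply to the study units; unit stay equals hospital stay; LOS exponential or lognormal with coefficient of variation (CV) 0.8 or 1.0.

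**Check against the plan's own count.** Mixed mean LOS = 0.54 × 6.6 + 0.46 × 5.31 = 6.01 days. For exponential LOS with mean μ, the share kept is P(μ) = 1 − (μ/T)(1 − e^(−T/μ)). Mixing the two groups with T = 30 gives 0.801. At full occupancy, 27 × 30/6.01 × 0.801 ≈ 108 and 22 × 30/6.01 × 0.801 ≈ 88 patients per unit-month, close to the stated 89 to 105. An exclusion of about 20% therefore fits the article's own planning.

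**Share dropped (T = 30.4, exponential).** P(5.31) = 0.826 and P(6.6) = 0.785, so 17.4% and 21.5% are dropped. The lognormal cases give 17-22%. Mean stay is 4.2-5.5 days in those kept and 8.6-12.9 days in those dropped.

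**LOS comparison.** The shift from 6.6 to 5.31 days (1.29 days) serves only as a test value.

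| LOS shape | Difference among those kept | Share lost |
|---|---|---|
| Exponential | 4.88 − 4.21 = 0.67 | 48% |
| Lognormal, CV 1.0 | 0.78 | 39% |
| Lognormal, CV 0.8 | 0.90 | 30% |

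If the BIT shortens stay only in patients with a behavioral diagnosis, by 10, 20 or 30% (exponential, T = 30), true arm differences of 0.36, 0.71 and 1.07 days appear as 0.17, 0.36 and 0.57: about half is lost. The loss can be larger when the shortening is confined to a small long-stay group. If only the 17.5% with events go from 8 to 6.4 days (others 5.5), the true 0.175 × 1.6 = 0.28 days appears as 0.11.

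**Composite.** Suppose event status is fixed and the BIT prevents no event. The event rate among those kept is 0.175·P(μe) / [0.175·P(μe) + 0.825·P(μo)], where μe and μo are the mean stays with and without an event. The article gives neither, so a range is used, with the overall mean held at 6.01 days in the control arm and T = 30.

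- μe = 6.6, cut by 10%: 17.1% control, 17.5% BIT, a gap of 0.4 points.
- μe = 12, cut by 30%: 13.7% control, 15.5% BIT, a gap of 1.7 points (before rounding the rates).

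Under the same models a true 5-point reduction appears as 2.7 to 4.6 points. If stays lengthen by 10%, the gap reverses: 0.4 to 0.5 points in favor of the BIT.

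**Effect of counting events to the crossover in all arrivals.** With μe = 8, μo = 5.5, event times uniform within the stay and T = 30.4, cutting event stays by 1 to 2 days gives 16.1% against 16.7-17.2% under the current rule, and 15.2% against 15.5-15.8% in all arrivals. About half of the spurious gap remains.

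**The case against.** The rule is deliberate, has a stated purpose and applies equally to both arms. If the BIT does not alter LOS, selection is non-differential and the comparison among short-stay patients is fair. The trial's hypothesis concerns disruptive behavior and staff perceptions; shorter stay is other centers' observation, and the Background itself calls most such reports anecdotal. If stays do shorten, the modelled bias runs against the BIT and so could not create a false claim of benefit. The composite shift of 0.4-1.7 points is also no larger than about one standard error of the arm difference (√[(0.175 × 0.825 + 0.125 × 0.875)/895] ≈ 1.7 points, ignoring clustering).

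Much of this stands. A reader might infer that the rule biases both comparisons outright; the documents support only a conditional statement. A reader might take 1.29 days as an expected arm effect; it is the gap between patients with and without a behavioral diagnosis. A reader might also conclude that patients transferred off the unit are lost, but discharge from the unit can be read to include transfer, so this is not established.

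What does not stand is that the point can be left alone. LOS was chosen as an outcome because it may respond, and when it does, the filter hides part of the response. Nor is the conservative direction guaranteed for the composite, since it reverses if stays lengthen.

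**Conclusion.** The concern holds in conditional form. The analysis set is defined by a post-exposure variable that is also a secondary outcome, and the article neither corrects nor acknowledges this. With no BIT effect on LOS, the arms remain comparable and the results simply describe shorter-stay patients. With an effect, the LOS comparison is right-truncated: about 17-22% of admissions are dropped and roughly 30-50% of the difference is lost. That range rests on the Background mean stays and the assumed LOS shapes, and the loss can be greater if only a long-stay minority benefits.

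For the composite, the distortion is smaller and less certain: about 0.4-1.7 points against a 5-point target, using event-to-LOS links that the article does not give. The case for changing the LOS analysis is therefore firm. For the composite, it supports an added analysis rather than replacement of the primary set.

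**What to change.** **LOS.** Replace the comparison of completed stays by an analysis of every patient arriving on a unit during a month, in the arm in force at arrival, as time to discharge censored at the crossover. The censoring date is then fixed by the calendar, and no patient contributes time under both conditions. Table 2 starts the clock at the order to admit, which can precede arrival on the unit, so the wording should either start the clock at arrival or treat earlier time as delayed entry.

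**Composite.** The current set may stay as primary to avoid mixed exposure. Add a prespecified analysis of all arrivals by arm at arrival, with events counted up to the crossover, for example as time to first event.

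**Discussion.** List selection on LOS among the threats to validity.

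**Cost.** A changed query and analysis wording; enrollment has ended, but the data are already in the electronic health record. Late-month arrivals have short follow-up. The composite rate counted to the crossover falls in simulation from 17.5% to about 15%, with some attenuation of the difference, and part of the selection effect on the composite remains.
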